### **4.2 Outcomes**

#### **Case Definition – Undiagnosed Stage 3 CKD**

Patients with undiagnosed stage 3A-3B CKD will be identified if they have no healthcare encounter with a diagnosis code for CKD at any time during the  $\geq 12$ -month lookback period before the first eGFR measurement and up to 6 months post-index date (baseline period). Those with a documented diagnosis of CKD during this time period will be considered as having diagnosed CKD. It will be assumed that patients with at least one diagnostic code for CKD during the above specified time window have diagnosed CKD. 错误!未找到引用源。 below shows the study schematic.

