- Diabetes mellitus
  - Type 1 diabetes (T1D)
  - Type 2 diabetes (T2D)
  - Unclassified diabetes
- Hypertension
- Glomerulonephritis
- Hyperkalemia
- Hypertensive kidney failure
- Diabetic nephropathy
- Acute kidney injury (using diagnostics codes)
- Unspecified kidney disease
- Gout
- Poly cystic kidney disease
- Lupus
- Number of clinic visits in the year before the index date

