### Sensitivity Analysis

To calculate the robustness of our undiagnosed CKD definition (identified through 2 eGFR measures and no ICD-9/10 CKD diagnosis codes, and OHDSI ICD-10 CN2016 is used in the CRDS database), we will conduct sensitivity analyses 1-2 that assess whether the lack of healthcare encounters, as originally defined, truly captures an undiagnosed population.

Sensitivity analysis for undiagnosed CKD includes ICD-9/10 diagnosis codes for stage 3 CKD or higher

Sensitivity analysis for undiagnosed CKD includes ICD-9/10 diagnosis codes for CKD based on a broader definition derived by Winkelmayr *et al.*, 2005 ([section 8](#)). We will conduct sensitivity analysis 3 to assess if we have included sufficient individuals with undiagnosed CKD in the database, as required by study inclusion [criteria 2](#).

Sensitivity analysis for adjustment of inclusion criteria 2 from “at least 12 months of continuous presence in the database or registration in the data prior to the first qualifying eGFR (for data sources with information on enrollment)” to “at least one medical visit with diagnostic record within  $\leq 12$  months prior to the first qualifying eGFR”. There are no changes in any other inclusion and exclusion criteria. Analyze undiagnosed CKD according to the primary study definitions using eGFR measures captured within a specific time period prior to diagnosis.

- *Time to CKD diagnosis*

For the cohort of patients with no CKD diagnosis code as of the study index date (cohort 2), the median (95% CI) time in days/months from the study index date to physician-diagnosed CKD (using the primary CKD study definition) will be calculated using the Kaplan-Meier method. Survival times will be censored as of the last day of follow-up for patients who remain undiagnosed by a physician. Time to physician diagnosis of CKD will be calculated overall and by patient characteristics and comorbidities. If possible, association between baseline characteristics and time to CKD diagnosis will be assessed using relevant regression models. The time to physician diagnosed stage 3 CKD or higher (sensitivity analysis #1) and the time to CKD using a broader definition (sensitivity analysis #2) ([section 8](#)) will also be calculated.

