## 8. APPENDICES

**Table A1. ICD-9/10 diagnosis coding definitions for identifying CKD**

| Description                                 | ICD-9                   | ICD-10                         | ICD-10CN2016#                                                                                                                                                                                                                   |
|---------------------------------------------|-------------------------|--------------------------------|---------------------------------------------------------------------------------------------------------------------------------------------------------------------------------------------------------------------------------|
| Primary Study Definition             |                         |                                |                                                                                                                                                                                                                                 |
| Chronic kidney disease, Stage (I)           | 585.1                   | N18, N18.1                     | N18, N18.801                                                                                                                                                                                                                    |
| Chronic kidney disease, Stage (II)          | 585.2                   | N18.2                          | N18.802                                                                                                                                                                                                                         |
| Chronic kidney disease, Stage (III)         | 585.3                   | N18.3, N18.30, N18.31, N18.32  | N18.803                                                                                                                                                                                                                         |
| Chronic kidney disease, Stage (IV) (severe) | 585.4                   | N18.4                          | N18.804                                                                                                                                                                                                                         |

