| Acute renal failure                 | 572.4, 580.xx, 584.xx, 580.0, 580.4, 580.89, 580.9, 582.4, 791.2, 791.3          | K76.7, N00.3, N01.3, N08, N00.8, N00.9, N17, N03.8, R82.3, R82.1                                                                                                                                                                         | K76.7, N00.3, N00.8, N00.9, N01.3, N03.8, N17, N17.0, N17.1, N17.2, N17.8, N17.9, R82.1, R82.3, N10.x00, N10.x01                                                                                                                                                                                                                                                                                                           |
| Miscellaneous                       | 274.10, 440.1, 442.1, 453.3, 581.xx, 593.xx, 753.0, 753.3, 866.00, 866.01, 866.1 | M10.3, I70.1, I72.2, I82.3, N04, N02.2, N08, N28.81, N28.83, N28.1, N13.5, N13.8, N13.4, N13.7, N28.80, N28.89, N28.82, N28.9, R80.2, Q60.2, Q60.5, Q63.0-Q63.8, S37.009, S37.019, S37.029, S37.039, S37.049, S37.059, S37.069, S31.001, | I70.1, I72.2, I82.3, M10.3, N02.2, N04, N04.0, N04.1, N04.2, N04.3, N04.4, N04.5, N04.6, N04.7, N04.8, N04.9, N08*, N13.4, N13.5, N13.7, N13.700, N13.701, N13.8, N28.1, N28.8, N28.807, N28.821, N28.812, N28.800, N28.9, Q60.2, Q60.5, Q63, Q63.0, Q63.1, Q63.2, Q63.3, Q63.8, Q63.9, R80, S31.0, S31.000, S37.0, S37.000, S37.001, S37.002, S37.003, S37.004, S37.010, S37.011, N07, N06, N12, N14, N15, N16*, Q61, N25 |

\* Adapted from Winkelmayr et al. (2005)

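### Sensitivity analysis 2 accepts a single acute or injury code as a CKD diagnosis, so its undiagnosed prevalence is only a lower bound and its time-to-CKD curve can accrue events with no CKD recorded

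*Protocol*

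**What the plan says.** Section 5.2 (Sensitivity Analysis) states that sensitivity analyses 1 and 2 test whether the primary definition identifies people who are truly undiagnosed. The second "includes ICD-9/10 diagnosis codes for CKD based on a broader definition", adapted from a published claims-data validation study. The paragraph on time to CKD diagnosis adds that "the time to CKD using a broader definition (sensitivity analysis #2" will also be calculated.

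The codes are in section 8, Table A1, titled "ICD-9/10 diagnosis coding definitions for identifying CKD". The rows shown for sensitivity analysis 2 are chronic renal insufficiency, hypertensive nephropathy, "Acute renal failure" and Miscellaneous. In the Chinese column the acute row includes "N17, N17.0, N17.1, N17.2, N17.8, N17.9", with K76.7, N00.x, N01.3, R82.x and N10.x00/N10.x01. The Miscellaneous row includes S37.x, S31.0 and N28.1.

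Section 4.2 sets the rule for using a list: "It will be assumed that patients with at least one diagnostic code for CKD during the above specified time window have diagnosed CKD". The protocol asks for no repeat code and no accompanying chronic code, and it plans no separate result without the non-chronic codes.

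**The concern.** The analysis is meant to find CKD that was recorded under a label missing from the primary list. A broader chronic code answers that question. An acute renal failure code, or a kidney injury code under S37.x, does not: it records an event and does not show that anyone recognised chronic disease.

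Followed as written, a patient whose only listed code is N17.9 becomes a diagnosed CKD case. In the time-to-event analysis, the same code after index is the diagnosis date. If undiagnosed prevalence falls clearly under sensitivity analysis 2, the reader cannot tell how much of the fall is CKD recorded elsewhere and how much is the coding of acute events. For the Kaplan-Meier curve the problem is sharper, because the curve would rise even in a cohort where CKD was never diagnosed.

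**Working it through.** **The plan's own figure.** Section 5.5 states a margin of ±3 points for n = 1,000 and prevalence of 60% to 80%. The half-width 1.96·√(p(1−p)/n) gives 3.04 points at p = 0.60 and 2.48 points at p = 0.80. The figure reproduces and is not in dispute. At the roughly 27,000 patients expected in CRDS (section 5.5), the half-width is 0.58 points at p = 0.60 and 0.48 points at p = 0.80.

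**Inputs not in the protocol.** No code frequencies are given. Let *a* be the share of primary-undiagnosed patients whose *only* sensitivity-2 codes are non-chronic. Patients who also carry a chronic code from the list are reclassified anyway and do not count towards *a*. Assumed range: 2% to 20%.

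**Prevalence.** If a share *b* is reclassified by chronic codes, the restricted list gives p(1−b) and the full list gives p(1−b−a). The part due to non-chronic codes is p·a:

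| a | from p = 60% | from p = 80% |
|---|---|---|
| 2% | 1.2 points | 1.6 points |
| 5% | 3.0 points | 4.0 points |
| 10% | 6.0 points | 8.0 points |
| 20% | 12.0 points | 16.0 points |

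At a = 5% the shift is about 5 times (3.0/0.58) to 8 times (4.0/0.48) the sampling half-width at n = 27,000.

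The direction is certain when the list is compared with itself minus the non-chronic codes. Reading it as a fall from the primary result also assumes that every primary code is kept. The rows shown for sensitivity analysis 2 do not repeat the primary diabetes row, so that is an assumption.

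**Time to CKD.** Assume constant rates, with non-chronic codes arriving at *r* per year. If CKD is never diagnosed, the curve still reaches 1−exp(−r·t). At t = 3 years this is 8.6%, 13.9% and 25.9% for r = 3%, 5% and 10%. If the true median time to a chronic code is M months, the apparent median is ln 2/(ln 2/M + r/12):

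| r per year | M = 24 months | M = 48 months |
|---|---|---|
| 2% | 22.7 | 43.0 |
| 5% | 21.0 | 37.3 |
| 10% | 18.6 | 30.4 |

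Both M and r are assumptions.

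**Overlap between rows.** The acute row is not purely acute. N03.8 is also in the chronic renal insufficiency row, and ICD-9 582.4 falls under that row's 582. Miscellaneous contains N25, which is in the primary list. Neither row can simply be deleted.

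**The case against.** The strongest defence is that the breadth is deliberate and disclosed. The definition is called broader and footnoted as adapted from a published list. Sensitivity analysis 1 narrows the primary definition and sensitivity analysis 2 widens it. Every patient already has two stage 3 eGFR values more than 90 days apart (section 3.4), so an acute code is not necessarily unrelated to recognised kidney disease. If undiagnosed prevalence stays high even under this list, the primary conclusion is strengthened. All of this stands, and it is why the full list should be kept. It does not rescue the time-to-CKD curve, and the protocol does not describe the prevalence as a lower bound.

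A reader might go further and infer that the protocol contradicts itself, because section 4.3.1 lists "Acute kidney injury (using diagnostics codes") among the comorbidities. That does not hold. The same list has hypertensive kidney failure and diabetic nephropathy, and corresponding categories are in the primary CKD code list. Section 4.4 also names acute kidney injury as an etiology of CKD.

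A reader might also infer very large falls by counting everyone with any acute code. That is the wrong group: only patients with no chronic sensitivity-2 code are moved by these codes. CRDS draws on Grade 3A hospitals and section 4.4 allows for inpatient eGFR values, which makes acute codes plausible here, but the protocol gives no figure for how common they are.

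Finally, it is fair to say that section 6.1 leaves statistical procedures and table shells to a later SAP. The code list and the one-code rule, however, are fixed in this protocol.

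**Conclusion.** The point holds for sensitivity analysis 2 only. As written, one acute or injury code counts as diagnosed CKD and as a Kaplan-Meier event. The prevalence is a lower bound relative to the same list limited to chronic codes, and the time-to-CKD curve can accrue events with no CKD recorded.

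The direction is certain and the size is not. Under the assumed 2-20%, the fall is 1.2 to 12 points from 60%, or 1.6 to 16 points from 80%. These are scenarios, not estimates.

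Two stronger conclusions are not supported. The primary prevalence and primary time to diagnosis are not affected, because the acute row is not in the primary list. Nor is the sensitivity-2 prevalence unreadable: it is informative as a lower bound, and it becomes ambiguous only if it falls substantially.

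**What to change.** 1. Keep the full adapted list, so that results stay comparable across countries, and label its undiagnosed prevalence a lower bound.
2. Add a restricted run of sensitivity analysis 2 for both prevalence and time to CKD. Drop the codes that appear only in the acute row, and drop the injury and other non-chronic codes in Miscellaneous (for example S37.x and S31.0). Keep any code that is also in the chronic row or the primary list, such as N03.8 and N25. List the retained codes in Table A1.
3. In section 5.2, base the statement on whether the definition captures truly undiagnosed patients, and any time-to-CKD statement, on the restricted run.

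Removing the acute row alone would not be enough, because Miscellaneous would still hold non-chronic codes. The cost is a code-by-code pass through two rows of Table A1, a rerun of an existing program and one extra output column.
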